### 2.*8*.2 Primary Analysis

The primary analysis will evaluate the effectiveness of the mind-mindedness training in improving outcomes for both caregivers and children immediately after the intervention. We will use linear regression models for each outcome, which includes caregiver mind-mindedness, child social anxiety (using SCAS-P), attachment insecurity (AISI), caregivers’ MM, and the Theory of Mind (ToM Task Battery). Each model will compare the post-intervention scores (Time 1) between the intervention and control groups, while controlling for baseline values (Time 0). All analyses will adhere to intention-to-treat principles. The effects of the intervention will be assessed using linear regression models, comparing outcomes at post-intervention (T1) and follow-up (T2) to baseline (T0), while controlling for baseline scores. When applicable, multiple imputation with 20 datasets will be used to address any missing data. Effect sizes will be reported using standardised beta coefficients and 95% confidence intervals.

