# 2. Materials and Methods

## 2.1 Objectives

The main aim of this study is to evaluate the efficacy of the caregiver's MM training in reducing social anxiety symptoms among preschool children. Additionally, to examine how culture (Iranian and British) moderates the relationship between caregivers’ MM training and reductions in social anxiety symptoms among preschool children.

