## 2.4 Participants

The study aims to recruit 100 primary caregivers (aged 18-60 years) of preschool-aged children (aged 4-7 years) who exhibit symptoms of social anxiety. Eligible participants must reside in either the United Kingdom or Iran. Caregivers whose children have existing clinical diagnoses or are currently receiving other forms of treatment or support will not be included in the study. Children will be included in the study based on symptoms of social anxiety reported by caregivers, assessed using the Spence Children’s Anxiety Scale – Parent Version (SCAS-P). Although the SCAS was initially validated for children aged 6 to 12 (63),it has been reliably utilised with younger children aged 4 to 6 in parent-report studies (Edwards et al., 2010). For this study, the inclusion criteria will specifically focus on elevated scores in the social phobia subscale. Those whose anxiety profiles indicate separation anxiety or general behavioural inhibition, rather than social anxiety, will be excluded during the screening process. Children with a confirmed clinical diagnosis, such as autism spectrum disorder, generalised anxiety disorder, or ADHD, along with those currently receiving psychological or educational treatment, will not be eligible for participation. The research team will not make any formal diagnoses; inclusion decisions will be based solely on parent-reported data obtained through the SCAS-P. This approach guarantees consistency across participants while focusing on observable symptoms rather than clinical labels.

Participants will be recruited through a combination of targeted outreach and community engagement strategies. This includes advertisements in preschools and nurseries, referrals from early years professionals, and word-of-mouth recommendations from other caregivers. The recruitment strategy is designed to ensure a demographically diverse yet diagnostically homogeneous sample of families, with equal representation from the UK and Iran.

Due to the nature of the intervention, participant blinding is not possible, as caregivers will be fully informed of their group allocation, either participating in mind-mindedness training sessions or joining a peer-support group. However, the assessors responsible for data collection and analysis, including those evaluating mind-mindedness, child social anxiety, attachment, and theory of mind, will remain blinded to the group allocations to ensure an unbiased evaluation of outcomes.

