### 2.*8*.3 Secondary Analyses

Secondary analyses will assess the persistence of intervention effects at the three-month follow-up (Time 2). Linear regression models will compare follow-up scores to baseline scores while controlling for baseline values. This analysis will provide evidence regarding the durability of the intervention outcomes.

Mediation Analysis: Path analysis using structural equation modelling will test whether attachment security and theory of mind mediate the relationship between MM training and child anxiety reduction. Model fit will be assessed using standard indices (CFI > 0.95, RMSEA < 0.06, SRMR < 0.08).

Moderation analyses will investigate the influence of cultural context (UK vs. Iran) by including interaction terms in multiple regression models. Additionally, exploratory correlational analyses will examine the relationships between changes in mind-mindedness, social anxiety, attachment, and Theory of Mind. In these analyses, effect sizes and confidence intervals will be reported alongside p-values. To manage the risk of Type I and Type II errors, false discovery rate (FDR) corrections will be applied using the Benjamini-Hochberg procedure where appropriate.

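### Four outcomes share primary status at two-sided 5% each, although the stated main aim is child social anxiety alone and no multiplicity rule is expressly assigned to them

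*Protocol*

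**What the plan says.** **Aim.** Section 2.1 of the protocol sets the main aim as testing "MM training in reducing social anxiety symptoms among preschool children". It adds culture as a moderator of that same effect.

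**Primary analysis.** Section 2.8.2 is directed at "improving outcomes for both caregivers and children immediately after the intervention". Its list of outcomes begins "We will use linear regression models for each outcome, which includes caregiver mind-mindedness, child social anxiety (using SCAS-P), attachment insecurity (AISI", names mind-mindedness a second time, and ends "and the Theory of Mind (ToM Task Battery". Each model compares T1 scores between groups with adjustment for T0. Later the same section speaks of "comparing outcomes at post-intervention (T1) and follow-up (T2) to baseline (T0), while controlling for baseline scores".

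**T2.** Section 2.8.3 places the three-month comparison among the secondary analyses.

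**Error control.** Section 2.8.4 sets a two-tailed 5% level for all analyses. The one multiplicity statement is the last sentence of section 2.8.3: "false discovery rate (FDR) corrections will be applied using the Benjamini-Hochberg procedure where appropriate".

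**Score.** Section 2.4 selects children so that "the inclusion criteria will specifically focus on elevated scores in the social phobia subscale". Sections 2.5 and 2.8.2 name the construct as child social anxiety measured by SCAS-P, and section 2.7 speaks of child anxiety. None of them says whether the outcome is the total score or the subscale.

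**The concern.** A trial with one main aim would normally have one outcome that decides whether the aim was met. Here the aim is single but the primary analysis is not. No section designates one primary outcome, and the sample-size section does not say which outcome it powers.

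Two things are at stake. First, four unadjusted looks give more than a 5% chance that some primary result is significant by chance. Second, the four outcomes do not carry the same weight for the aim. Mind-mindedness is what the sessions teach (section 2.6). A trial with no effect on social anxiety but a change in mind-mindedness would still contain a significant result under the primary heading, with nothing in the protocol to say that the main question was answered in the negative.

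The unstated SCAS-P score leaves one more choice open, on the outcome that matters most.

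**Working it through.** **1. The plan's own figure.** Section 2.8.1 states two predictors, f² = 0.15, alpha 0.05, power 0.80 and a minimum of 89 participants. I used the noncentral F distribution with λ = f²N and denominator df = N − 3.

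- Both predictors tested jointly, 80% power: N = 68.
- Group coefficient alone, 80% power: N = 55.
- Group coefficient alone, 95% power: N = 89.

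So 89 does not follow from the stated inputs. That is a separate matter. What counts here is whether 89 contains an allowance for four outcomes. At 0.05/4 = 0.0125 the required N is 78 (group coefficient) or 94 (joint test), so it does not appear to.

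**2. Number of primary tests.** Section 2.8.2 has five entries and one is a repeat, which leaves four distinct outcomes at T1.

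**3. Chance of at least one false positive, no true effect on any outcome.**

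- Independent tests: 1 − (1 − 0.05)⁴ = 1 − 0.8145 = 18.5%.
- Correlated tests: for each outcome Z = √r × (shared normal) + √(1 − r) × (own normal), counting draws in which any |Z| exceeds 1.96, over 1,000,000 draws. The documents give no correlations, so r is an assumption.

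| Assumed r | At least one of four significant |
| --- | --- |
| 0 | 18.5% |
| 0.3 | about 17% |
| 0.5 | about 16% |
| 0.8 | about 11% |

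**4. If mind-mindedness truly changes.** The three remaining outcomes then carry the risk: 1 − 0.95³ = 14.3% if independent.

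**5. What each remedy does to power.** With 100 recruited and 10–15% attrition, 100 × 0.85 = 85 to 100 × 0.90 = 90 are evaluable. At f² = 0.15:

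| Remedy | Alpha per test | Power, group coefficient | Power, joint test |
| --- | --- | --- | --- |
| One primary outcome | 0.05 | 94–95% | 89–91% |
| Four primaries, Bonferroni | 0.0125 | 84–87% | 75–78% |

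Naming one outcome leaves alpha where the sample-size section put it, so that route needs no further participants.

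**The case against.** **There is an error-control rule.** A reader might infer that the trial has none at all. The protocol does not support that. The Benjamini-Hochberg sentence is not expressly limited to secondary analyses, and only its position suggests that it is. An analysis plan that is not at hand could define its family. What stands is that the protocol assigns no rule to the four primary tests. If the rule were extended to them, it would hold the error at 5% when no outcome responds (independent or positively dependent tests), but not otherwise. With a clear true effect on mind-mindedness, the smallest of the other three p-values is compared with 2 × 0.05/4 = 0.025, and the chance of a false positive among them is at least 1 − 0.975³ = 7.3% if independent.

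**Eight tests rather than four.** One could count T1 and T2 together: 1 − 0.95⁸ = 33.7%. But the opening of section 2.8.2, its description of each model and section 2.8.3 all make T1 primary. The T2 phrase is better read as a drafting inconsistency, so the figures for four tests apply.

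**Power.** It is tempting to say that the sample is too small for four outcomes. Each test is planned and run at 5%, so no mismatch arises per test. Even after a Bonferroni split, a test of the group coefficient keeps more than the planned 80%. Only the joint test falls below it.

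**The outcome is identified.** The construct is named as child social anxiety, so it would be wrong to call the outcome undefined. Only the score is open, and that detail alone could be left to an analysis plan.

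**Roles and success rule.** Section 2.8.3 treats attachment and theory of mind as mediators, which implies some ranking. The protocol also states no success rule, so a claim of success on any one outcome is a possibility that it leaves open, not one that it announces. But implied roles do not undo the explicit primary label in section 2.8.2.

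**Conclusion.** The point holds in this form: section 2.8.2 gives four outcomes equal primary status at two-sided 5% each, against a main aim that concerns one of them, and no multiplicity rule is expressly attached to them. The chance of at least one false-positive primary result at T1 is 18.5% if the tests are independent. It is about 11% to 17% over assumed correlations of 0.8 to 0.3, at least twice the nominal 5% throughout. These figures assume equal pairwise correlations, no true effect on any outcome, and no adjustment of the primary tests.

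This is more than detail left for later. The protocol itself applies the primary label to all four outcomes and puts T2 under both headings, so an analysis plan could put it right only by departing from the protocol. The unstated SCAS-P score is a lesser gap, but it should be closed at the same time because it concerns the outcome that carries the main aim.

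**What to change.** 1. In section 2.8.2, name one primary outcome: child social anxiety on SCAS-P at T1, compared between groups with adjustment for T0, at two-sided 5%.
2. State the score. The social phobia subscale fits both the aim in section 2.1 and the selection rule in section 2.4. Use the same term in sections 2.5, 2.7 and 2.8.2.
3. Move mind-mindedness, AISI and Theory of Mind to section 2.8.3, and delete the second mention of mind-mindedness.
4. Remove T2 from section 2.8.2, so that every T2 comparison is secondary.
5. Apply Benjamini-Hochberg to that named secondary family, in place of the open qualifier. The family is three outcomes at T1 plus four at T2, seven tests in all. Say whether the moderation and mediation tests belong to it.
6. State in section 2.8.1 that the sample size refers to the primary outcome.

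The change should be dated and made before anyone sees outcomes by group. It costs protocol wording only: alpha stays at 5% and no larger sample is needed. The small downside is that the other three outcomes can no longer be claimed as primary. Keeping all four with a Bonferroni split is possible but lowers power, to 75–78% if the joint test is the one intended.

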### 2.*8*.3 Secondary Analyses

Secondary analyses will assess the persistence of intervention effects at the three-month follow-up (Time 2). Linear regression models will compare follow-up scores to baseline scores while controlling for baseline values. This analysis will provide evidence regarding the durability of the intervention outcomes.

Mediation Analysis: Path analysis using structural equation modelling will test whether attachment security and theory of mind mediate the relationship between MM training and child anxiety reduction. Model fit will be assessed using standard indices (CFI > 0.95, RMSEA < 0.06, SRMR < 0.08).

Moderation analyses will investigate the influence of cultural context (UK vs. Iran) by including interaction terms in multiple regression models. Additionally, exploratory correlational analyses will examine the relationships between changes in mind-mindedness, social anxiety, attachment, and Theory of Mind. In these analyses, effect sizes and confidence intervals will be reported alongside p-values. To manage the risk of Type I and Type II errors, false discovery rate (FDR) corrections will be applied using the Benjamini-Hochberg procedure where appropriate.

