## 2.8 Statistical methods

### 2.*8*.1 Sample Size and Power

A power analysis was conducted in advance using G*Power 3.1 to determine the necessary sample size for linear regression models with two predictors: group assignment and baseline score. Assuming a medium effect size (f² = 0.15), an alpha level of 0.05, and a power of 0.80, the analysis indicated that a minimum sample size of 89 participants is required. To account for an expected attrition rate of approximately 10–15%, we plan to recruit 100 participants, with 50 participants in each group. These participants will be evenly distributed between the United Kingdom and Iran. This target is deemed feasible and suitable for an early-phase efficacy trial. The sample is designed to provide sufficient power for testing the primary effects of the intervention using regression-based methods, while maintaining enough power for within-group analyses.

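### The 3-month durability analysis is worded as follow-up against baseline and names no between-group contrast, so as written it cannot show that an intervention effect persists.

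*Protocol*

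**What the plan says.** The protocol describes the contrast of interest in three places, and they do not agree.

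- **Section 2.8.2, T1, first statement.** "Each model will compare the post-intervention scores (Time 1) between the intervention and control groups", adjusted for the T0 value. This is the randomised contrast.
- **Section 2.8.2, T1 and T2, second statement.** Intervention effects are to be assessed by linear regression, "comparing outcomes at post-intervention (T1) and follow-up (T2) to baseline (T0), while controlling for baseline scores". The reference is now baseline, and the control group is not mentioned.
- **Section 2.8.3, T2.** "Linear regression models will compare follow-up scores to baseline scores while controlling for baseline values". The inference follows directly: "This analysis will provide evidence regarding the durability of the intervention outcomes".

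Three other statements bear on how these are read. Section 2.8.1 bases the power calculation on a regression with group and baseline score as its two predictors, without tying that model to a time point. The same section says the sample was chosen "while maintaining enough power for within-group analyses". Section 2.4 says that "the inclusion criteria will specifically focus on elevated scores in the social phobia subscale" of the SCAS-P, and section 2.5 makes the SCAS-P the child anxiety outcome. No section states an intervention-versus-control comparison at T2.

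**The concern.** Persistence of an intervention effect is a difference between randomised groups at 3 months. A comparison of T2 with T0 measures change over time, which mixes any effect with everything else that moves scores in both arms. Two such sources are plausible here:

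- **SCAS-P.** Children enter because a SCAS-P subscale score is high. If that score also serves as T0, scores tend to fall on retest without any intervention.
- **Theory of Mind and similar outcomes.** Children aged 4 to 7 develop over three months, and the same tasks are given three times.

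The sentence is also not a definable model. Comparing T2 with T0 while conditioning on T0 leaves no obvious coefficient to report as the effect, so an analyst would have to choose one. One available choice, a pre-post test within the training arm, would be reported as durability without the protection of randomisation. This is not detail left for a later analysis plan: the protocol states a T2 contrast, twice, and it is not the one its conclusion needs.

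**Working it through.** **No figure to reproduce.** The protocol gives no number for the T2 analysis. The check is what the written contrast would yield with no effect in either arm.

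**Inputs from the protocol.** 50 children per arm; 10-15% attrition, so 42.5 to 45 completers per arm (44 used below); two-sided 5% level; selection on an elevated SCAS-P subscale.

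**Assumptions, because the protocol does not give them.** Entry cut-off c (in population SDs), T0-to-T2 correlation r, and whether the screening score is the T0 score. The within-arm paired test is itself only one possible reading.

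**Case A: the screening score is T0.** For a standard normal score selected above c, let m be the mean and v the variance after selection.

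- c = 0: m = 0.798, v = 0.363.
- c = 1: m = 1.525, v = 0.199.
- Expected fall = (1 − r)·m.
- SD of change = √[(1 − r)²·v + 1 − r²].
- Noncentrality = (fall ÷ SD)·√44, referred to a noncentral t with 43 df.

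| Cut-off | r | Fall (SD) | SD of change | Noncentrality | P(significant), no effect |
|---|---|---|---|---|---|
| mean | 0.6 | 0.319 | 0.836 | 2.53 | 0.70 |
| mean | 0.7 | 0.239 | 0.737 | 2.16 | 0.56 |
| mean | 0.8 | 0.160 | 0.612 | 1.73 | 0.39 |
| +1 SD | 0.6 | 0.610 | 0.820 | 4.94 | 0.998 |
| +1 SD | 0.7 | 0.458 | 0.727 | 4.18 | 0.983 |
| +1 SD | 0.8 | 0.305 | 0.607 | 3.34 | 0.903 |

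**Case B: T0 is measured separately after screening.** Let a be the correlation of screening with T0, and b that of screening with T2.

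- Expected fall = (a − b)·m.
- Variance of change = 2(1 − r) − (a − b)²(1 − v).
- With c = 1, a = 0.8, b = 0.7, r = 0.7: fall = 0.1 × 1.525 = 0.153, SD = 0.769, noncentrality = 1.31, P = 0.25.
- With a = b the fall is zero and P = 0.05.

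**The between-group model under the same conditions.** T2 was regressed on group and T0 in simulated trials with no effect (45 per arm, 3,000 runs per scenario, cut-offs at 0, +1 and +1.5 SD, r from 0.6 to 0.8, screening score as T0). The group coefficient was significant in 4.2-5.5% of trials, which is nominal within simulation error.

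**Power of that model.** With 85 to 90 completers in total and the protocol's f² = 0.15, applied to the group coefficient, power is 94-95%.

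**The case against.** The strongest reply is that a group term was simply left out of a sentence. Section 2.8.1 names group and baseline score as the predictors, section 2.8.2 introduces the T1/T2 sentence as assessing effects of the intervention and places all analyses under intention to treat, and section 2.8.3 sets out to assess persistence of those effects. A regression that adjusts for baseline is not a paired pre-post test. On that reading the control arm already absorbs regression to the mean and maturation. The remark on within-group power is not tied to T2 or to any efficacy claim.

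Much of this stands, and it limits what can be claimed. A reader might infer that the protocol prescribes a pre-post test and that a worthless intervention would almost certainly look durable. The documents do not support that: the sentence is incoherent rather than a clear paired test. The 90-99.8% range also needs a +1 SD cut-off and the screening score as T0, neither of which is stated.

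The mechanism is narrower than it may seem. Selection is on the social phobia subscale, while the outcome is given as SCAS-P with no subscale named, so a full-scale outcome would regress less. Mind-mindedness, AISI and Theory of Mind are not selection variables. For them the problem is shared change of other kinds.

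The reply does not supply a T2 group contrast. None is written anywhere, and the two T1 statements in section 2.8.2 conflict whatever was intended.

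**Conclusion.** The T2 analysis is wrong as written and needs correcting. Sections 2.8.2 and 2.8.3 state a follow-up-versus-baseline comparison, name no group contrast at T2, and draw a conclusion about durability that only a between-group comparison can support. The intention may well be a baseline-adjusted group comparison, in which case the defect is one of wording, but the text does not say so.

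That conclusion does not depend on the assumed inputs; the size of the consequence does. If the wording were carried out within one arm with the screening score as T0, the false-positive rate on SCAS-P would lie between about 39% and 99.8% over the cut-offs and correlations tabulated. With a separate T0 it was 25% in the one example and falls to 5% when screening correlates equally with T0 and T2. The first statement of the primary T1 contrast is sound, and the problem at T1 is only that the later sentence contradicts it.

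**What to change.** - **Section 2.8.3:** replace the T2 sentence with wording such as: T2 scores will be compared between the randomised groups by regression of the T2 score on group and T0 score; the group coefficient with its 95% confidence interval estimates the effect at 3 months.
- **Section 2.8.2:** delete the reference to comparison with baseline, so that T1 and T2 use the same between-group model.
- **Within-arm change:** report descriptively only, with no tests and no efficacy wording.
- **Country:** if the randomisation stratifier is added as a covariate, add it to both the T1 and T2 models, so that no new mismatch arises.

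The cost is a few sentences of protocol text. The data, software and sample size stay as planned.

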### 2.*8*.4 Data Management

Data will be collected electronically using REDCap, ensuring standardised collection and secure storage. Quality assurance measures will include double data entry verification for 20% of cases, automated range checks, weekly backups, and monthly data integrity audits to identify patterns of missing data. All analyses will be conducted using Stata 17.0 (StataCorp, College Station, TX) with a significance level of p < 0.05 (two-tailed). Results will be reported following CONSORT guidelines for randomised trials.

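### The exploratory change-score correlations name no adjustment for arm or country; if pooled across arms, they can show a link that is only the treatment effect seen twice

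*Protocol*

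**What the plan says.** Protocol section 2.8.3 (Secondary Analyses) lists, after the mediation and moderation analyses, that "exploratory correlational analyses will examine the relationships between changes in mind-mindedness, social anxiety, attachment, and Theory of Mind". Effect sizes, confidence intervals and p-values are to be reported, with Benjamini-Hochberg correction where appropriate. Section 2.8.4 sets a two-sided 5% level for all analyses.

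No arm term, country term or analysis set is given for these correlations. Elsewhere the plan names such terms when it wants them. In section 2.8.2, "Each model will compare the post-intervention scores (Time 1) between the intervention and control groups", with the baseline value as a covariate. The moderation analysis in 2.8.3 adds interaction terms for country.

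The Abstract (Discussion) hypothesises that training raises mind-mindedness and lowers child social anxiety relative to control. Section 1.1 expects the benefit to come through better attachment security and theory of mind. So the plan expects training to move all four of the variables to be correlated.

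**The concern.** Arm is a common cause of any two changes that training affects. Suppose the training arm gains on mind-mindedness and falls on anxiety, while the control arm does neither. Plotted together, the arms form two clouds displaced along a diagonal, and the correlation over all participants is negative even if each cloud on its own has no slope. The same holds for country if average change differs between the UK and Iran. Section 3 allows for this by saying that culture may affect how the intervention is received and how well it works.

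What is at stake is interpretation. The induced correlation has the sign that the theory predicts, so a reader could take it as showing that caregivers who gained more in mind-mindedness had children whose anxiety fell more. A pooled correlation cannot separate that from the arm difference already estimated in the primary models. Benjamini-Hochberg addresses the number of tests, not confounding by arm.

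**Working it through.** **Inputs from the protocol**
- Sample size: "we plan to recruit 100 participants, with 50 participants in each group" (2.8.1). Stated attrition of 10–15% leaves 85–90.
- Effect size: "Assuming a medium effect size (f² = 0.15), an alpha level of 0.05, and a power of 0.80" (2.8.1), for "linear regression models with two predictors: group assignment and baseline score".
- Test level: two-sided 0.05 (2.8.4).

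**Assumptions, not in the protocol**
- Correlation within arms is zero. This is the null case of interest.
- Change scores have unit variance within arms, and standardised arm effects d1 and d2 are varied over a range.
- For the reference case, f² is assigned wholly to arm and carried over to both change scores. With 1:1 allocation f² = d²/4, so d = 2·√0.15 = 0.775.

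**The plan's own figure.** The protocol concludes that "a minimum sample size of 89 participants is required". With the noncentral F distribution (noncentrality f²·N), the stated inputs give 68 for the joint test of two predictors and 55 for a single coefficient. The 89 is therefore not reproduced. That is a separate matter: only N = 100, its reduction by attrition, and f² are used below.

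**Size of the induced correlation.** With 1:1 arms, the between-arm part of the covariance is −d1·d2/4 (one variable rises, the other falls), and each variance becomes 1 + d²/4. Hence

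r = −(d1·d2/4) / √[(1 + d1²/4)(1 + d2²/4)].

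- d1 = d2 = 0.775: r = −0.15/1.15 = −0.13.
- d1 = d2 = 0.5: r = −0.0625/1.0625 = −0.06.
- d1 = d2 = 1: r = −0.25/1.25 = −0.20.
- Either d = 0: r = 0.

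**How often it is significant.** Simulation with 20,000 trials per setting, no link within arms, N = 100:

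| d1, d2 | mean pooled r | pooled, significant | adjusted for arm, significant |
|---|---|---|---|
| 0.8, 0 | 0.00 | 4.9% | 4.9% |
| 0.5, 0.2 | −0.02 | 5.8% | 5.0% |
| 0.5, 0.5 | −0.06 | 9% | 5.1% |
| 0.775, 0.5 | −0.09 | 14% | 5.1% |
| 0.775, 0.775 | −0.13 | 25% | 5.1% |
| 1, 1 | −0.20 | 53% | 4.9% |

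After attrition, the 0.775/0.775 case gives 23% at N = 90 and 22% at N = 86.

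**Country.** Take 0.775/0.775 at N = 100 and add an assumed 0.5 SD country difference in both changes, aligned with the arm pattern. The pooled test is significant in about 42% of trials, adjustment for arm alone leaves about 9%, and adjustment for arm and country gives about 5%. If the country differences run against the arm pattern, the pooled rate is about 10–11%. The 0.5 SD is illustrative only. It shows why country belongs in the adjustment together with arm.

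**The case against.** The strongest objection is that pooling is not in the text. Section 2.8.3 does not say that the correlations are simple, unadjusted or taken over all participants. Section 2.8.1 mentions power for analyses within groups, section 2.5 collects demographic data to control for confounding, and an analysis plan that is not shown may settle the matter. This stands in part: it would be wrong to report that the protocol states whole-sample correlations. But neither of those two remarks is tied to these correlations. The protocol has already chosen the method (correlating changes, with p-values) and names covariates elsewhere when it wants them, so the natural reading is a pooled bivariate correlation.

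A second objection is that the pooled correlation really is non-zero in the scenario above, so rejecting zero is an error only if the question concerns association within arms. That is formally right. However, only the within-arm association would add anything to the between-arm comparison already planned.

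A third is that little depends on the result. The analysis is labelled exploratory, and the mechanism has its own path analysis. This stands, and it is why the severity is low.

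A reader might also infer that a successful trial would produce these links automatically. The figures do not support that. Both variables must respond to training; a trial that moved only one would show no artefact. Even in the 0.775/0.775 case about three trials in four would show no significant pooled correlation.

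**Conclusion.** The point holds in conditional form. The protocol plans correlations between changes, with p-values and no stated adjustment for arm or country. If they are run across both arms, they are biased towards the hypothesised link whenever training affects both variables of a pair. With no within-arm association, the chance of a significant result at N = 100 is 5% if either variable is unaffected, about 9% with 0.5 SD on both, and about 25% with 0.775 SD on both (22–23% at N = 86–90). It passes one half only when both effects are about 1 SD.

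These rates rest on assumed effects on the change scores. The 0.775 SD is not a figure in the plan; it follows from f² = 0.15 only if all of f² is credited to arm and the same effect applies to both changes. The planned primary comparisons are not affected. This is a cheap improvement of low severity.

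**What to change.** In section 2.8.3, replace the change-score correlations with partial correlations, or with regressions of one T1 score on the other, adjusted for arm, country and the T0 values of both measures. State that the results are interpreted as associations within arms. Keep the exploratory label and the Benjamini-Hochberg step.

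The cost is one sentence and a few degrees of freedom (four covariates, out of roughly 85–100 participants). No new data are needed, and the sample size and primary analysis do not change. The change should be made before any outcome data are analysed.
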